## Background

Musculoskeletal pain causing sick-leave is multifactorial and may or may not have a negative effect on work participation. Sick leave has serious consequences for the individuals who take sick leave due to their pain, and it is fundamental for them to find ways to prevent or reduce their pain or, at least learn to cope with it [1].

Patient-oriented rehabilitation among individuals with work disability is a major challenge for municipalities in Denmark as they have principal responsibility for this function. In 2008 and 2009 respectively there were 687 and 757 new applications for sickness benefits due to disorders in the back and upper body in the Sonderborg Municipality. These disorders often include complex and diffuse symptoms that, over time, can result in chronicity and loss of function. Pain-related sick leave, particularly amongst younger workers, is often based on symptoms that are rarely consistent with a specific disease [2].

A study has shown that the interaction between the characteristics of the sick-listed, the company they are employed by and the municipality has important influence on return to work. In addition, economic conditions and sickness absence policies in society influence the number and length of absences, as well as the risk of being dismissed [3].

Individual factors, such as age, obesity, smoking, manual materials handling, lack of job control, lung restriction and reduced work ability have all been shown to be risk factors for sick leave [4]. Poorly perceived health status is associated with an extended duration of sick leave, and self-perceived health status can also predict return to work for persons with musculoskeletal complaints [5,6].

A systematic review of interventions for work-related complaints in the arm, neck and shoulder has shown limited evidence for the efficacy of physical exercises in patients with nonspecific work-related upper extremity musculoskeletal disorders compared with no treatment or as add-on treatment. Currently, there is no scientifically reported difference in the effects of various types of physical exercises on pain and pain coping [7]. Nor have solution-focused interventions delivered by psychologists been more effective than ‘treatment as usual’ for return to work or improvement in perceived health [8].

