### Outcome measures

Measurements will take place at baseline and after 3 months at the end of the intervention. A secondary follow-up measurement will be performed 12 months after baseline to examine long-term effects. Baseline demographic characteristics of participants will also be recorded.

The *primary endpoint* for efficacy will be the participants’ sick-listed status (yes/no) as registered by the Department of Financial Security in the Sonderborg Municipality. As a *co-primary endpoint,* the duration of the sickness absence within the evaluation period will be examined.

Secondary endpoints will include anthropometric measures, hand-grip strength and aerobic capacity. In addition, we will evaluate musculoskeletal symptoms, general health, work ability, physical capacity, kinesiophobia, physical functional status, interpersonal problems and mental disorders, via self-reported questionnaires.

*Anthropometric measurements* will be performed by trained physiotherapists. Weight, height and circumference of waist and hip will be measured.

*Hand-grip strength* will be measured in kilograms with a digital hand-held dynamometer. Participants will be instructed to sit upright on a chair with the safety strap around their wrist, with their arm at right angles and their elbow by the side of their body. Wrist extension only up to 30° will be allowed. The participants will be strongly encouraged to squeeze with maximum effort. Three trials will be recorded and an extra trial will be conducted if force is changed more than three kilograms compared with a previous attempt [22].

*Aerobic capacity* will be estimated with the Aastrand-Rhyming Test, which is a submaximal cycle ergometer aerobic fitness test. The participants will cycle 60 rpm at a work load set at a level referenced to the sex and condition of the subject. The participant’s HR is measured during the exercise and the test will be terminated when the subject reaches a steady state HR of between 120 and 160 beats/min, with a change of less than 5 beats between two consecutive minutes. Aerobic capacity will be estimated based on Aastrands nomogram, using the participant’s work-load and HR during testing [23]. Finally, the result will be adjusted for age and gender and normalised to body weight.

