*Musculoskeletal symptoms* in the shoulder, elbow, hand, neck, upper back and lower back will be evaluated with a modified version of the Nordic Musculoskeletal Questionnaire. The questions used are “Have you, at any time during the last 3 months had trouble (such as ache, pain, discomfort) in [body part]?” (yes/no), “How many days have you had trouble (such as ache, pain, discomfort) in [body part] during the last 3 months?” (0 days, 1–7 days, 8–30 days, 30 days but not every day, every day), “How many days in total have you been on sick leave because of trouble (such as ache, pain, discomfort) in [body part] during the last 3 months?” (0 days, 1–7 days, 8–30 days, 30 days), “Because of trouble (such as ache, pain, discomfort) in [body part] have you been examined or treated by a doctor, chiropractor or physiotherapist or the like during the last 3 months (yes/no), “Have you had trouble (such as ache, pain, discomfort) in [body part] during the last 7 days?” (yes/no). Illustrations from the Nordic Questionnaire define the respective body regions of the neck, right shoulder, left shoulder, upper spine, lower spine, right elbow, left elbow, right hand and left hand [24].

*General health and health-related quality of life* will be measured using the SF-36 Health Survey, a standardised questionnaire investigating eight health concepts: physical functioning, role limitations because of physical functioning, bodily pain, general health, vitality, social functioning, role limitation because of emotional problems and mental health. Answers are recorded using a Likert scale [25,26].

*Work ability* will be assessed by the single-item measure that was originally part of the widely used Workability Index. However, recent studies have shown that the single item question is a reliable and easy tool with validity comparable with the full index [27]. The question used is “Imagine that your work ability is worth 10 points when it is at its best. How many points would you give your present work ability?” A numerical rating scale was used where 0 represents “not able to work” and 10 represents “the highest work ability” [28].

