### Statistical analysis

All participants who receive a group allocation will be included for efficacy and feasibility (intention-to-treat population). The primary outcome, differences across the groups in the proportion of participants who are not sick-listed at 3 and 12 months, will be calculated using a Chi-squared test (and 95 confidence intervals). Also, the rate of return to work at 3 months (co-primary outcome measure), will be calculated based on the number of days with sickness absence as recorded by the Department of Financial Security in Sonderborg Municipality. We will compare the time on sick leave across the groups using the Kaplan-Meier method and report the median time on sick leave with a 95% confidence interval. A Cox proportional hazard model will be used to measure the effectiveness of TPA and CPSMP relative to REF, which will be reported as hazard rate ratio (HRR) with a 95% confidence interval. Participant characteristics that vary amongst the three groups at baseline will be included in a multivariate Cox proportional hazard model to control for their potential confounding effect.

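### The multivariate Cox model takes its covariates from chance baseline imbalance and so gains essentially no precision; a short prognostic list fixed in advance would

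*Protocol article*

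**What the plan says.** The Statistical analysis section treats the co-primary endpoint in three steps. It gives Kaplan-Meier medians by arm. Then "A Cox proportional hazard model will be used to measure the effectiveness of TPA and CPSMP relative to REF", reported as a hazard rate ratio (HRR) with its confidence interval. Then comes the adjusted model: "Participant characteristics that vary amongst the three groups at baseline will be included in a multivariate Cox proportional hazard model". The reason given is "to control for their potential confounding effect".

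No covariate is named, no criterion for varying is given, and nothing says whether the unadjusted or the adjusted HRR is the main result.

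The endpoint is set in Outcome measures, where "the duration of the sickness absence within the evaluation period will be examined" as co-primary. The primary endpoint, sick-listed status at 3 and 12 months, is compared by a chi-squared test without covariates.

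The Background names candidate predictors. Age and obesity are among the factors listed there, and "lack of job control, lung restriction and reduced work ability have all been shown to be risk factors for sick leave". It adds that "self-perceived health status can also predict return to work for persons with musculoskeletal complaints". Outcome measures shows that body measurements, a single-item 0–10 work ability score, the SF-36 and baseline demographics are collected. None is designated as a covariate. The recruitment and randomisation section describes permuted blocks of 3 and 6 and states no stratification factors.

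**The concern.** In a randomised comparison, a baseline difference between arms is chance and not confounding in the usual sense. Picking covariates because they differ has three consequences.

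- It selects on imbalance, not on prognosis. An irrelevant variable that happens to differ gets in; a strong predictor that happens to balance stays out.
- The model is known only once the baseline data are in, and then only after someone decides what counts as varying.
- The main benefit of adjustment in a trial, explaining outcome variation to sharpen the treatment comparison, is mostly lost.

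In a Cox model, an HRR conditional on covariates is also not the same quantity as the unadjusted one. What the adjusted HRR measures therefore shifts with whichever variables enter. At stake are the precision and interpretability of one reported result for a co-primary endpoint.

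**Working it through.** **Inputs from the protocol article.** Return to work by 3 months 43% (REF) and 70% (TPA), 46 per group, two-sided alpha 0.05 (Sample size); three arms, at least 138 participants (Abstract). The number of characteristics, the screening threshold and the predictors' strength are not given. They are assumptions below.

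**1. The plan's own figure.** With mean proportion 0.565, the pooled formula gives n = [1.96·√(2·0.565·0.435) + 0.842·√(0.70·0.30 + 0.43·0.57)]² / 0.27² = (1.374 + 0.568)² / 0.0729 ≈ 51.7, so 52 per group, not 46. Power at 46 is Φ[(0.27·√46 − 1.374)/0.675] = Φ(0.68) ≈ 75%. That is a separate matter; here it only shows that precision is not in surplus.

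**2. The same rates on the Cox scale.** With exponential times, HR = ln(0.30)/ln(0.57) = 2.14. Events in TPA plus REF: 46·(0.70 + 0.43) ≈ 52. Schoenfeld power = Φ[√(52/4)·ln 2.14 − 1.96] ≈ Φ(0.79) ≈ 78%.

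**3. How often chance selects something.** For k independent characteristics screened at level a, the probability of at least one selection is 1 − (1 − a)^k. With k = 15 and a = 0.05: 1 − 0.95^15 = 54%. Range:

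| k | a = 0.05 | a = 0.10 |
|---|---|---|
| 5 | 23% | 41% |
| 10 | 40% | 65% |
| 15 | 54% | 79% |
| 20 | 64% | 88% |
| 30 | 79% | 96% |

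Three true predictors are all missed with probability 0.95³ = 86%.

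**4. Effect on power.** Simulated trials: 46 per arm, exponential times, censoring at 3 months, marginal rates held at 43% and 70%. Selection is by one-way ANOVA across the three arms at p < 0.05, from 15 candidates (rows with three predictors) or from the true predictors plus 16 irrelevant ones (other rows). Power for TPA versus REF, in %:

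| True predictors, log-HR per SD | Trials | No adjustment | Imbalance rule | Prespecified |
|---|---|---|---|---|
| 3 at 0.3 | 1,200 | 80 | 80 | 86 |
| 3 at 0.5 | 1,200 | 81 | 81 | 93 |
| 3 at 0.3 | 1,500 | 78 | not run | 85 |
| 3 at 0.5 | 1,500 | 78 | not run | 91 |
| 2 at 0.2 | 5,000 | 78.1 | 77.3 | 79.9 |
| 2 at 0.3 | 5,000 | 77.4 | 76.6 | 82.1 |
| 4 at 0.2 | 5,000 | 77.9 | 77.0 | 81.6 |
| 4 at 0.3 | 2,000 | 79.1 | 79.0 | 87.2 |
| 4 at 0.4 | 2,000 | 80.0 | 80.1 | 92.0 |
| 4 at 0.5 | 2,000 | 80.4 | 80.9 | 95.6 |

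Monte Carlo standard error at 80% power is √(0.8·0.2/1,200) ≈ 1.2 points for 1,200 trials and 0.6 for 5,000. The imbalance rule stays within 1 point of no adjustment throughout. Prespecified adjustment gains 6–13 points with three predictors and about 2–15 over the wider grid. Loosening the screen to p < 0.10 does not help: with four predictors at 0.3, power is 78.3% with none, 76.8% with the rule and 85.4% prespecified.

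**5. Type I error** (four predictors, 2,000 null trials per setting). Imbalance rule 3.6–4.6%, no adjustment 3.9–5.0%, prespecified 4.4–5.4%. Reporting the better of the unadjusted and imbalance-adjusted results gives 4.4–6.2%, at most 1.2 points above the unadjusted test in the same runs.

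**The case against.** **Scope.** The primary test has no covariates, and an HRR without covariates is described before the multivariate model. Read in order, the adjusted model looks like an additional analysis. This stands, and it limits the point to the adjusted HRR. The text does not say which HRR leads, however, so the order of sentences does not settle it.

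**No false-positive harm.** A reader might infer that data-dependent covariates inflate type I error. They do not here: selection uses baseline data and not outcomes, and step 5 shows rates at or slightly below 5%. The rule is also written in advance; only the covariate set depends on the data. The small excess arises only if the better of two results is reported, which the protocol does not say it will do.

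**A larger power loss.** A reader might hold 2.14 as the hazard ratio conditional on three predictors. Simulation then gives 69% (log-HR 0.3) and 57% (0.5) without adjustment, against 77% and 76% prespecified, a gain of up to 19 points. The documents do not support this as the trial's power: at 0.5 it implies about 46% versus 67% returning to work, a smaller effect than the stated 43% versus 70%.

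**Assumed inputs.** The 15 characteristics, the 5% screen and the predictors' strength are not in the protocol. This stands. They size the effect but do not create it: the imbalance rule gained nothing material in any setting.

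**Availability.** The Background ties age and work ability to sick leave, and only perceived health directly to return to work. Age is not itemised among the measurements, and smoking, job control, manual handling and lung restriction are not listed as measured. This stands and restricts the candidate list.

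**Conclusion.** The point holds for the adjusted Cox HRR of the co-primary endpoint and for nothing else. The protocol does not merely leave the covariates open; it states a rule, and the rule selects on chance imbalance with an undefined criterion. The cost is forgone precision and an adjusted result whose content cannot be known in advance.

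On the protocol's own rates, a prespecified set of three predictors would raise Cox power from about 78–81% to about 85–93%, given log-HRs of 0.3–0.5 per SD. The gain falls to about 2 points if predictors are few and weak, and reaches about 15 if they are more numerous and strong. These figures also assume exponential times and independent, normally distributed covariates.

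Nothing here invalidates a planned test. In particular, the unadjusted chi-squared analysis is valid and needs no covariate-adjusted counterpart on this account. This is a free improvement.

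**What to change.** Replace the covariate sentence with a short list of prognostic variables fixed before outcome data are seen and included whatever the observed balance. Candidates are age, baseline work ability score, SF-36 general health and, if the municipal register gives it, days sick-listed at enrolment. Four covariates against about 52 events in TPA plus REF is 13 events per covariate, a modest load. Remove selection by baseline difference and the confounding rationale. State whether the adjusted or the unadjusted HRR is the main Cox result, and report the other as supportive.

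Cost: a wording change in the protocol or the SAP. Work ability and the SF-36 are already collected, age is presumably among the demographics, and prior absence should be obtainable because the same municipal department records sickness-absence days. No new measurement or additional participant is needed.

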## Discussion

This study will contribute to evidence-based recommendations regarding initiatives for citizens who are sick-listed due to pain that is related to the back or the upper body.

Rehabilitation of people with work disability is a major challenge for municipalities when pain causes loss of function and the citizens receive sickness benefits because they cannot maintain their participation in the labor market. Pain-related sick leave amongst younger workers, is often based on symptoms that are rarely consistent with a specific disease [2].

After the Danish Local Government Reform in 2007, and embodied in the Health Act, the patient- and citizen-oriented rehabilitation is a joint responsibility of Denmark’s 98 municipalities and 5 regions and it is an important aspect of strengthening prevention of long-term work disability. Besides the 71 municipalities in Denmark which offer general patient education programmes developed by the Stanford University School of Medicine, there are other methods of group-based patient education that are widely used that also involve health care professionals as teachers [14]. But the organisation of patient education is complicated by the effects of such programs being largely unknown [15]. On the other hand, preventive strategies in the workplace aimed at enhancing physical capacity and/or the ability to cope with musculoskeletal pain have been successfully tested [9,10,16,17,44,45] but their efficacy with respect to return to work has not been investigated. Accordingly, the municipalities will be the primary beneficiaries of the results from this investigation of intervention programmes for sick-listed citizens.
